### Assessment Procedures

This study will conduct data collection at 3 different time points: TI—baseline, TII—postintervention for group 1 and preintervention for group 2 (8 weeks), and TIII—follow-up for group 1 and postintervention for group 2 (16 weeks). Participants will complete web-based self-reported surveys administered via Qualtrics (Qualtrics). If the participant prefers, paper surveys will be administered. Figure 2 lists study measures and assessment points.

**Figure 2 figure2:**
[figure not shown]
Schedule of enrollment, interventions, and assessments.

### Primary Outcome Measures

#### Depression Symptoms

Depression symptoms will be assessed with the PHQ-9 [42].

#### Psychiatric Distress

Psychiatric distress will be measured using the depression and anxiety subscales of the Brief Symptom Inventory [45].

### Secondary Outcome Measures

#### Perceived Stress

Using the Perceived Stress Scale-4 [46], perceived stress will be investigated.

#### Facets of Mindfulness

The Five Facet Mindfulness Questionnaire [47] will be used to assess self-reported mindfulness. In total, the 5 subscales include (1) nonreactivity, (2) observing, (3) describing, (4) nonjudgment, and (5) acting with awareness.

### Possible Mediators

#### Extent of Mindfulness Self-Practice

Participants will be asked the following questions: “Besides the sessions you may have attended as part of this study, on your own, ‘Did you engage in mindfulness meditation or other mindfulness practices in the past two months (8 weeks)?’ ‘How many days per week did you engage in mindfulness meditation or other mindfulness practices?’ ‘How long in minutes did you meditate per session of mindfulness meditation?’ ‘Describe your practice of mindfulness (what exercises/activities/techniques did you practice?).’” For quantitative analyses, we will use the variable representing the number of days of mindfulness practice per week.

#### Executive Functioning

The 20-item self-reported Deficits in Executive Functioning Scale, Short Form will be used [48].

### Participant Characteristics and Possible Moderators

#### Demographics

We will assess age, gender, race, ethnicity, marital status, language spoken, educational attainment, employment status, annual household income, health insurance status, and current smoking status.

#### Treatment History

Mental health treatment history will be assessed using the Adult Service Use Schedule [49-51].

#### Trauma History

Adverse life events and trauma history will be assessed with the Adverse Childhood Experiences Questionnaire [52] and Life Events Checklist for the *DSM-5* (*Diagnostic and Statistical Manual of Mental Disorders* [Fifth Edition]) [53].

#### Baseline Depression Symptoms

The PHQ-9 [42] will be used to assess baseline depression symptoms. Participants will be subdivided into mild depression (scores less than or equal to 10) or moderate to severe depression (scores greater than 10) for subgroup comparisons.

### Feasibility Outcomes

#### Retention and Attendance

Retention and attendance will be assessed via the number of sessions attended and the percentage of participants who completed all sessions.

#### Engagement

Engagement will be measured per the items described above that assess the frequency and extent of mindfulness practice.

#### Satisfaction With Treatment

Treatment satisfaction and perceived utility of treatment will be assessed with the Treatment Satisfaction Survey [54] adapted for our study. This version will reflect how participants are satisfied with and respond to the MBCT intervention.

#### Format Delivered via the Web

To determine the feasibility of the web-based format, participants will be asked about strengths, weaknesses, and areas for improvement.

### Sample Size

The total sample size of our trial is expected to be 128 individuals with 64 participants placed into each group. This was estimated by a 2-tailed *t* test using GPower 3.1 (Informer Technologies, Inc) software. Our calculation of sample size depended on (1) the level of significance (α error probability), which was set as .05 based on Ronald A Fisher’s suggestion [55]; (2) the expected effect size, which was set as *d*=0.5, according to Cohen classification that “a medium effect of .5 is visible to the naked eye of a careful observer” [56]; (3) the expected power of this study (1–β error probability), which was set as 0.8 based on Cohen theory [57] because we failed to obtain support from previous similar studies; and (4) the allocation ratio (N2/N1), for which we expect number of participant in treatment group and control group to be the same.

### Randomization

Consenting participants will be randomized 1:1 to either group 1 or group 2 via the randomization function found in Qualtrics. This will be conducted by the principal investigator (PI). Once the number of participants has reached 7-12 individuals for both group 1 and group 2, this study will commence. This will proceed continuously until the expected sample size of 128 individuals is reached, or 4 years have elapsed. The implementation of this process will be overseen by the clinical research team.

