#### Intervention Procedures

The intervention will be delivered by 3 Licensed Clinical Social Workers who have previously undergone MBCT teacher training and become certified instructors. The intervention will consist of 8 weekly 2-hour group therapy sessions. All sessions will be delivered to a group of up to 12 participants and will take place over Zoom (Zoom Video Communications, Inc). The minimum number of participants needed to proceed with each intervention program is 7 individuals. Certified instructors will follow the standardized MBCT protocol developed by Segal et al [43] (see Textbox 1 for the outline of each session).

Mindfulness-based cognitive therapy program outline per Segal et al [43].Session 1: Awareness and automatic pilotSession 2: Living in our headsSession 3: Gathering the scattered mindSession 4: Recognizing aversionSession 5: Allowing or letting beSession 6: Thoughts are not factsSession 7: How can I best take care of myself?Session 8: Maintaining and extending new learning

MBCT integrates training in mindfulness meditation and cognitive-behavioral methods. It teaches skills designed to increase awareness of internal reactions that trigger depressive symptoms, such as depression-related rumination and negative thoughts, and provides techniques to detach from these dysfunctional cognitive processes [19]. In the first half of the program, participants will focus on learning the principal tenets of mindfulness. They will explore central themes about the tendencies of the mind to habitually engage with thoughts, which produces an array of feelings and emotions. In the latter half of the program, participants will begin the practice of becoming aware of thoughts as they arise, thereby witnessing habitual patterns that may lead to unpleasant feelings or emotions [43]. Outside of the sessions, participants will be assigned daily homework exercises and given handouts as well as audio recordings to use in their mindfulness practice. Participants who miss a session will be contacted by the research team to determine if they would benefit from medical or psychiatric assistance and to assess any barriers to upcoming sessions.

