### Blinding

Blinding in this type of study is not possible, as knowledge of the group assignment to the participants and providers will be evident. However, to minimize bias in this study, the investigators as well as data analysts will be masked from the respective assignments of the intervention group and TAU group. Blinding will only be terminated after all data collection and analysis have been completed.

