### Data Monitoring Plan

By the National Institutes of Health Office of Human Research Protection, the research team has constructed the Data and Safety Monitoring Plan, safeguarding the well-being and privacy of study participants. Recruitment and safety data will be regularly reviewed by the monitoring board comprised of members from Prisma Health System and Clemson University. Using a personal code that is only accessible by the PI, each participant’s demographic data, and outcome measures will be linked and stored for data analysis. No other identifying data relating to the participant will be linked to these codes. If there are data that are missing, these will also be a component of the monitoring plan for statistical analyses. Every quarter, the board will convene to assess any adverse effects, and on an annual basis, the board will discuss the audition of trial conduct. If the trial needs to be halted, and after consulting the data monitoring committee, the PI will make the final decision to stop all trial proceedings.

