### Data Collection and Management

The clinical data collection team will receive training from a licensed clinical psychologist on appropriately gathering data from the PHQ-9 [42] forms to ensure the validity and reliability of trial data. All data collected will be stored electronically and encrypted to ensure confidentiality. This will be done at the clinical facility at which the data are collected. The PI will have full access to the trial data set. To promote the retention of participants, intervention facilitators will encourage continued participation in MBCT sessions, providing the stage to voice any concerns that may have arisen. If concerns arise regarding participation, a member of the research team will reach out to that participant to encourage them to remain.

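### The PI conducts the randomisation although the investigators are declared masked, and the 7–12 start rule is exposed whichever way the unnamed randomisation type is read

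*Protocol article*

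**What the plan says.** On allocation, the Randomization section of the protocol article states: "Consenting participants will be randomized 1:1 to either group 1 or group 2 via the randomization function found in Qualtrics". Of this step it says "This will be conducted by the principal investigator (PI"). The start rule follows: "Once the number of participants has reached 7-12 individuals for both group 1 and group 2, this study will commence". Cohorts then repeat: "This will proceed continuously until the expected sample size of 128 individuals is reached, or 4 years have elapsed".

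The Intervention Procedures section confirms both limits of the window. It sets a minimum of 7 per programme, and for the maximum it says "All sessions will be delivered to a group of up to 12 participants".

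On masking, the Blinding section accepts that participants and providers will know the assignment. It then says "the investigators as well as data analysts will be masked from the respective assignments of the intervention group and TAU group", and that this lasts until all data have been collected and analysed.

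Two other sections describe the PI's access. The Data Monitoring Plan links each participant's demographic and outcome data "Using a personal code that is only accessible by the PI". Data Collection and Management adds: "The PI will have full access to the trial data set".

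**The concern.** There are two separate problems.

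The first is a contradiction in the text. The PI is one of the investigators and performs the allocation, so the PI knows who went where. A masking statement that covers the investigators without exception therefore claims a protection that the procedure rules out. This matters because participants and providers are openly unmasked and the outcomes are self-report surveys. Concealed allocation and a masked analyst are most of the protection that remains.

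The second is the fit between the allocation and the start rule. Both arms must land between 7 and 12 before a cohort begins. Unrestricted draws can overfill one arm while the other is still short. A scheme that keeps the counts level avoids this, but makes upcoming assignments easier to foresee for the person running it, who here is the PI. In either case the design could be open to selection at entry, to loss between allocation and start, or to improvised handling of the surplus person.

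**Working it through.** **Masking: the sections side by side**

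- Randomization: the PI carries out the allocation.
- Blinding: investigators are masked until the end of analysis, and no one is excepted.
- These cannot both be true of the PI. The conclusion needs no assumption about the randomisation type.
- The sole access to the personal code and the full access to the data set support this but do not prove it. The code is described as linking demographic and outcome data, not allocation, and no timing is given for the data access.

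**The plan's own figure**

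The Sample Size section gives 128 (64 per group) for a two-sided t test with d = 0.5, α = 0.05 and power 0.80. The noncentral t calculation gives 63.77 per group, rounded up to 64, with power 0.801. The figure reproduces and is not in dispute.

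**Window: if the draws are independent at 1:1**

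Assumptions: people are allocated one at a time with probability 0.5, and each cohort starts from zero. The article states neither.

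- The window fails when one arm takes its 13th person while the other holds 6 or fewer. This is equivalent to one arm having 6 or fewer after 19 draws (13 + 6 = 19).
- P(fail) = 2 × P(Bin(19, 0.5) ≤ 6) = 2 × 43,796 / 524,288 = 0.167, or 1 in 6.0.
- A simulation of 100,000 cohorts gave 0.168.

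If instead a fixed batch is put through unrestricted draws together, the chance that the split falls outside 7–12 in both arms is:

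| Batch size | P(outside window) |
|---|---|
| 14 | 0.79 |
| 16 | 0.45 |
| 19 | 0.167 |
| 20 | 0.26 |
| 24 | 0.84 |

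So 0.167 is the most favourable value under unrestricted draws.

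**Window: if the counts are forced even**

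- Simulated permuted blocks of 2, 4, 6 and 8 gave no overflow (20,000 cohorts each). The largest arm seen was 9.
- The price is predictability. If counts are levelled after every pair, for example, each second assignment follows from the first, so half of all assignments are known in advance to someone who sees the running counts. Longer blocks reduce this share, but the last assignment in each block stays fixed.

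**Does overall imbalance matter?**

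- Under independent draws, one arm of 128 lies between 53 and 75 with about 95% probability.
- At d = 0.5 and two-sided α = 0.05, power is 0.790 at 53/75 against 0.801 at 64/64. The loss is about 0.01.

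**The case against.** The best reply is that most of the second problem rests on something the article does not say. It gives a 1:1 ratio and a software function, not coin-flip allocation, and the Sample Size section expects equal arms, which fits a balanced setting at least as well. A condensed article may leave sequence details to the full protocol. The two harms also largely exclude each other: independent draws can overflow but cannot be predicted, while balanced draws can be predicted but do not overflow. All of this stands, so the 17% is conditional and the two readings must be kept apart.

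A reader might infer more, and the documents do not support it:

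- *That people will be moved between arms.* No section says so. A 13th person could wait for the next cohort in the same arm, which would preserve the random allocation and the intention-to-treat comparison.
- *That most trials run this way would see a failure.* Compounding 0.167 over 6 to 10 cohorts gives 0.67 to 0.84, but only if every cohort starts from zero. Carrying people over breaks that assumption.
- *That early entrants wait for months knowing their arm.* The article does not say when participants are told. Recruitment opened in December 2022 and the first cohort's data were collected in January 2023, so a long wait is not a general feature.
- *That the PI selects whom to enrol.* Screening is by a member of the research team, and it is people who have already consented who are randomised.

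None of this touches the masking contradiction. It could be said that self-reported outcomes limit the effect of an unmasked PI on measurement. That is fair, but the statement remains untrue as written.

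**Conclusion.** The concern holds in two parts of different strength.

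The masking claim is contradicted by the article's own allocation procedure, and this rests on the text alone. The Randomization and Blinding sections must be reconciled.

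The start rule is exposed under either reading of the Qualtrics function. With independent draws, about 17% of cohorts starting from zero overfill one arm before the other can start, and the article states no handling. With forced balance, overflow goes but the next allocation is often foreseeable to the PI. How often depends on the block length and on whether the PI sees the running counts.

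Selection bias and differential loss before the start remain possible exposures. Nothing in the article shows that either has occurred, and overall imbalance is of no practical consequence for power. The point should be corrected, but it does not by itself invalidate the comparison.

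**What to change.** 1. Obtain consent and complete the baseline assessment first. When a cohort of 14–24 is assembled, randomise it in one step into equal halves from a pre-generated list. Halves of 14–24 always give 7–12 per arm (an odd total differs by one), so overflow cannot arise and there is no sequence of single assignments to predict.
2. Have the list held and run by an existing team member who neither screens nor analyses, in place of the PI.
3. In the Blinding section, limit the masking claim to those actually masked, such as the data analyst working with coded arms, and state that the PI is not masked if the PI keeps any role in allocation.

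No stratification is needed for this purpose, and the models already carry a cluster effect.

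The cost is a change of procedure and wording with the same tools and staff. The downside is that participants learn their arm later. With 30 enrolled by November 2023, up to 98 of the 128 allocations (128 − 30) came after that date and could benefit where still to be made. For allocations already made, the masking statement still needs correcting and the method used should be reported.

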### Blinding

Blinding in this type of study is not possible, as knowledge of the group assignment to the participants and providers will be evident. However, to minimize bias in this study, the investigators as well as data analysts will be masked from the respective assignments of the intervention group and TAU group. Blinding will only be terminated after all data collection and analysis have been completed.

### Statistical Methods

#### Primary Outcomes

An intent-to-treat method will be used to conduct the primary analyses. By comparing the baseline and demographic variables between groups, the randomization success will be determined. With a random intercept for a cluster of individuals, generalized linear mixed effects models (GLMMs) will be used [58] to assess the effects of MBCT on depression and psychiatric distress symptoms (hypothesis 1). Week 8 will be the primary end point for this assessment. The covariates measured at TI that are relevant but not balanced between group 1 and group 2 will be incorporated into all models. Additionally, all analysis models will include clinical site level as a fixed effect. GLMMs will be used to test the association between MBCT psychiatric distress (hypothesis 2), in addition to gains sustained at an 8-week follow-up (hypothesis 3).

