## Methods

### Study Design

Our study plans to examine how MBCT delivered via the web may affect primary and secondary outcomes for individuals with a history of depression. It will also assess mediators, moderators, and the sustainability of the intervention. The following hypotheses will be assessed among program participants in the intervention group as compared to a waitlist control group, and within groups compared from pre- to postintervention.

The MBCT intervention group will show a greater reduction in depressive symptoms from TI to TII, compared to the waitlist group.The MBCT intervention group will show a greater reduction in psychiatric distress symptoms from TI to TII compared to the waitlist group.The MBCT intervention group will sustain gains through the 8-week follow-up period at TIII.The MBCT intervention will improve secondary outcomes, such as:perceived stressfacets of mindfulnessThe MBCT intervention will improve the skills associated with mechanisms of change for individuals with a history of depression, and these skills will act as mediators between MBCT and primary and secondary outcomes:extent of mindfulness self-practiceexecutive functioning skillsThe format delivered via the web will meet feasibility aims measured by adherence, retention, attendance, and engagement.

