### Trial Design

Using a waitlist control design, this trial will randomize 128 eligible participants into 2 groups. In the first phase lasting 8 weeks, group 1 will partake in the MBCT intervention plus treatment as usual (MBCT + TAU) while group 2 will remain as waitlist control following TAU. In the second phase lasting 8 weeks, group 2 will begin completing the MBCT intervention, and group 1 will enter a follow-up phase, continuing with TAU. TAU will be comprised of psychotherapy, pharmacotherapy, or a combination of both. Data collection will be completed at baseline, 8 weeks (postintervention for group 1 and preintervention for group 2), and 16 weeks (follow-up for group 1 and postintervention for group 2). In this manner, our study design will ensure that both trial arms are treated fairly, and that group 1 can be followed up for 8 weeks to assess the sustainability of the intervention. Figure 1 outlines the flow of this study. The registration of this trial took place on April 22, 2022.

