#### Secondary Outcomes, Moderators, and Mediators

GLMMs will be used to assess the association between MBCT and the secondary outcomes of perceived stress and mindfulness skills (hypothesis 4). Potential moderators of the effect of MBCT, namely treatment history, traumatic life events history, baseline depression, and their interaction with MBCT, will be looked at in their own GLMMs. Using regression coefficients, the role of moderators that these variables may play will be assessed.

Using the PROCESS macro [59] in SAS (SAS Institute), the mediators, extent of mindfulness self-practice, and executive functioning skills (hypothesis 5), will be examined via the product of the coefficient method. This will be limited to the first phase of this study lasting 8 weeks. Further, 2 separate GLMMs will be used to assess how the primary and secondary outcomes may be indirectly influenced by MBCT. By regressing the mediator and outcome, respectively, on MBCT, and controlling for the mediators as well as applicable covariates, the indirect effects of MBCT on outcomes will be examined. Parallel multiple mediator models in addition to serial multiple mediator models will be used to conduct sensitivity analysis. To examine if MBCT effects will be sustained through 8 weeks postintervention (hypothesis 3), linear mixed-effects models will be used with main effects consisting of treatment group, time, group × time interaction, and nested random effects for subjects and cluster. A regression parameter associated with group × time interaction at 0 will be the null hypothesis. This acts as an equivalent for assessing the carryover effect [60]. If rejected, there is support that the effects of the intervention remain after 8 weeks have elapsed. An imputation method will be used to address any data that are missing.

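### The primary model's one random intercept has no defined level and does not match the nested model for hypothesis 3, so week-8 standard errors could be too small, too large or about right

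*Protocol article*

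**What the plan says.** Protocol article, Statistical Methods, Primary Outcomes, gives the model for depression and psychiatric distress: "With a random intercept for a cluster of individuals, generalized linear mixed effects models (GLMMs) will be used". The time point is fixed: "Week 8 will be the primary end point for this assessment". TI covariates come in only if they are relevant and prove unbalanced. No time term is named for these two outcomes.

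Other sections bear on what the intercept has to represent:

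- Study Design, hypothesis 1: "The MBCT intervention group will show a greater reduction in depressive symptoms from TI to TII, compared to the waitlist group". Hypothesis 2 has the same form for psychiatric distress.
- Intervention Procedures: "All sessions will be delivered to a group of up to 12 participants", and "The minimum number of participants needed to proceed with each intervention program is 7 individuals".
- Trial Design, phase I: "group 2 will remain as waitlist control following TAU".
- Randomization: "Once the number of participants has reached 7-12 individuals for both group 1 and group 2, this study will commence".
- Secondary Outcomes, Moderators, and Mediators: the hypothesis 3 model has group, time and their interaction, with "nested random effects for subjects and cluster". Hypothesis 3 also appears among the GLMMs under Primary Outcomes, so it is described twice.

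**The concern.** Two sources of correlation are present at week 8. Each person is measured at TI and TII, and MBCT participants share a therapy group while waitlist participants do not. The hypothesis 3 model treats subject and cluster as separate levels. The primary model names one level and leaves it undefined.

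This is the model for both primary outcomes. If the intercept stands for the participant, correlation within therapy groups is left out and the standard error is too small. If it stands for the therapy group and both time points are outcomes, within-person correlation is left out and the standard error of the change contrast is too large. Two analysts could follow the text faithfully and report different confidence intervals from the same data.

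**Working it through.** **Plan's own figure.** Two-sided α = 0.05, power 0.80, d = 0.5, 1:1 (Sample Size). The normal approximation gives 2(1.960 + 0.842)²/0.5² = 62.8, so 63 per arm. The exact noncentral t calculation gives 64 per arm, 128 in total, power 0.801. The stated 128 is reproduced. It contains no clustering term.

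**Inputs.** From the article: 64 per arm and therapy groups of m = 7 to 12, hence about 64/12 ≈ 5.3 to 64/7 ≈ 9.1 groups, or roughly 6 to 9. Assumed, because the article gives neither: therapy-group ICC 0.01 to 0.10 and TI-TII correlation ρ 0.4 to 0.7. Scores are in SD units.

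**Reading 1: participant intercept only.** Clustering exists in the MBCT arm alone. With DE = 1 + (m − 1)ICC, the ratio of true to reported SE is r = √((DE + 1)/2), and type I error is 2Φ(−1.96/r).

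| ICC | m = 7: DE, r, type I error | m = 12: DE, r, type I error |
|---|---|---|
| 0.01 | 1.06, 1.015, 5.3% | 1.11, 1.027, 5.6% |
| 0.05 | 1.30, 1.072, 6.8% | 1.55, 1.129, 8.3% |
| 0.10 | 1.60, 1.140, 8.6% | 2.10, 1.245, 11.5% |

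On change scores the true variance is 4(1 − ρ)/64 + ICC(m − 1)/64. At ρ = 0.6, ICC 0.02 and m = 7 this is 0.0250 + 0.0019 = 0.0269, so r = √(0.0269/0.0250) = 1.037 and type I error is 5.9%. At ICC 0.10 and m = 12 it is 0.0250 + 0.0172 = 0.0422, r = 1.299, type I error 13.1%. The top end is higher here because the ICC is expressed on single-score variance: change variance is 2(1 − 0.6) = 0.8, so 0.10 is 0.125 of it.

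**Reading 2: therapy-group intercept only, TI and TII both as outcomes.** Reported SE of group × time is √(4/64) = 0.25. The true SE, with therapy-group variance neglected, is √(4(1 − ρ)/64). The ratio is 1/√(1 − ρ).

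| ρ | True SE | Reported/true | Type I error |
|---|---|---|---|
| 0.4 | 0.194 | 1.29 | 1.1% |
| 0.6 | 0.158 | 1.58 | 0.2% |
| 0.7 | 0.137 | 1.83 | 0.03% |

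Power at d = 0.5: significance needs an estimate above 1.96 × 0.25 = 0.49. At ρ = 0.6, Φ((0.50 − 0.49)/0.158) = Φ(0.063) = 52.5%; over the range of ρ it is 52-53%. A simulation of 300 trials at ρ = 0.6 gave mean reported SE 0.246, empirical SD 0.158 and power 57%, against 87% for participant-level change. The simulation error of the 57% is √(0.57 × 0.43/300) ≈ 2.9 points, so it agrees broadly with the formula.

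**Reading 3: therapy-group intercept, one week-8 or change record per person.** No participant intercept is needed. With balanced clusters, a common intercept variance in both arms and true clustering in the MBCT arm only (40,000 simulated trials per setting), the reported SE is 1.01-1.10 times the true one. Type I error is 1.7-4.3% with cluster-based degrees of freedom and 4.0-6.8% with a normal reference. In a further simulation with 8 groups of 8 per arm, a partially nested model moved type I error from 2.6-4.1% to 3.9-4.7% and raised power by 2-5 points.

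**Coding of waitlist participants.** As an illustration under a therapy-group intercept, take ICC 0.05, 7 therapy groups (m = 64/7 = 9.14) and all 64 controls coded as one cluster. True variance is (1/64)(1 + 8.14 × 0.05) + 1/64 = 0.0220 + 0.0156 = 0.0376, SE 0.194. Model variance is 0.0220 + (0.05 + 0.95/64) = 0.0868, SE 0.295, about 1.5 times too large.

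**Baseline adjustment.** Always adjusting week 8 for its TI score multiplies the SE by √(1 − ρ²). At ρ = 0.6 this is 0.80, a 20% reduction.

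**The case against.** The strongest reply is that Reading 3 is the natural one. The section stresses week 8, treats TI measures as covariates and names no time term. Hypotheses about reduction can be tested with a change score or a baseline-adjusted week-8 score, so they do not force stacking. On that view the hypothesis 3 model has an extra subject level because it is longitudinal, and the two sections need not conflict. A group of people is also the ordinary meaning of the cluster phrase, which makes Reading 1 somewhat strained. All this stands. A reader might infer that the standard errors are wrong however the sentence is read; the article does not support that.

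A reader might also infer that both arms are modelled as clustered. The article never says how waitlist participants are coded. Recruitment batches of 7 to 12 form in both arms, and in the balanced single-record case a common intercept does little harm.

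It can also be said that cluster definitions and degrees of freedom belong in a full protocol or SAP. As omissions they would be no finding. But the article does state a random-effects structure, for both primary outcomes, and states it differently for hypothesis 3. Reading 3 is sound only with two choices the text does not make: one record per person, and a sensible coding of waitlist participants.

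**Conclusion.** The point holds as an undefined and inconsistently described random-effect level in the primary model. Depending on the reading, week-8 standard errors are too small (type I error about 5-13% for assumed ICC 0.01-0.10), too large (1.3-1.8 times for assumed ρ 0.4-0.7, power about 52%), or about right and mildly conservative. None of these sizes can be narrowed from the article, which gives neither an ICC nor a TI-TII correlation.

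The 52% applies only to the stacked reading without a participant term. It might be taken to mean that most of the planned power is lost, but a fall from 80% to 52% is about a third. The planned 80% also refers to a two-sample t test; at ρ = 0.6 the like-for-like comparison is with 87%.

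**What to change.** Reconcile the Primary Outcomes section with the hypothesis 3 model, and describe hypothesis 3 once. For both primary outcomes, state:

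- the outcome as the week-8 score, always adjusted for its TI value whether or not that value is balanced; or TI and TII as outcomes with a participant random intercept;
- a therapy-group random effect that applies only to the MBCT arm in phase I, with each waitlist participant as a singleton;
- Kenward-Roger or Satterthwaite degrees of freedom, since only about 6 to 9 therapy groups are expected in that arm.

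This costs protocol and SAP wording only; the design and data collection do not change. Intervals become wider than if therapy groups were ignored, by the factor r under Reading 1: 1.5-2.7% at ICC 0.01 and 7-13% at ICC 0.05. Baseline adjustment works in the other direction. One practical point: a therapy-group code present in one arm only shows a masked analyst which arm is MBCT, so the model should be fixed in writing before outcome data are examined.
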